### 2. Aims

(1) To evaluate the feasibility and efficacy of EMA-based smoking cessation intervention for smoking cessation

(2) To analyze the association between smoking cues and smoking-related behaviors in the local context. Smoking cues include exposure to POS tobacco displays, health warnings, scenes of others' smoking, alcohol use, social gathering, media items on promoting smoking cessation, feeling stressed/depressed, and other smoking-related cues. Smoking-related behaviors include purchase of tobacco, tobacco consumption, and nicotine craving.

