***Pilot study*** I have conducted a pilot study (first in Asia) to examine the feasibility of using low-intensity EMA for documenting smoking cues and smoking-related behaviors (See additional materials). In total, 302 smokers installed the EMA app (designed by the primary investigator) in their own smartphone for a 2-day data collection and contributed 1,744 EMA (48% of all EMA prompts) and 693 valid EMA pairs for further analysis. The completion rate of 4+ and 6+ EMA pairs in the overall participants was 29.1% and 13.2%, respectively. Findings showed that exposure to tobacco point-of-sale (POS) displays (odds ratio [OR]=19.55,  $p<.01$ ) and health warnings (OR=14.27,  $p<0.02$ ) were significantly associated with subsequent purchase of tobacco, consistent with other EMA observational studies. Exposure to the POS displays apparently led to subsequent craving (OR=1.57) and tobacco consumption (OR=1.47), but the sample size was not sufficient to show statistical significance. Findings were presented in the International Symposium on Digital Health 2019 (20).

During Jan 2020 to Oct 2020, I conducted another pilot study using EMA to investigate exposure to alcohol advertisements and alcohol drinking culture in university students. Participants completed 5 regularly prompted EMA surveys with an EMA app in their smartphone every day for 14 consecutive days. The results showed that the 48 participants responded in 2474 EMA (73.5% of all EMA prompts). The compliance rate of 49+ (70%) and 56+ (80%) EMA was 70.8% and 45.8%, respectively.

These two pilot studies suggests several improvements to increase the EMA compliance: (1) Complicated steps to set up an EMA schedule with the EMA app increase participants' burden in real-world participation. Future app development should reduce these complicated steps and use a more user-friendly interface. A simpler set-up procedure can also save recruitment time for each participant in the outdoor environment, as their available time for recruitment is limited. (2) To sustain a higher EMA compliance for time-based system-triggered EMA, separate assessments (in the alcohol EMA pilot study) is more preferred than pair-based assessments (in the tobacco pilot

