## **7. Subjects**

This proposed study aims to recruit daily tobacco users, regardless of intention to quit. We shall send mass emails to the University of Hong Kong (HKU) staff and students, post recruitment advertisements in media and smoking cessation clinics, or actively invite smokers at outdoor smoking hotspots to participate. Outdoor smoking hotspots (i.e., urban places with a butt

collector and a cluster of smokers) were shown as feasible platforms for efficient smokers' recruitment (21). The inclusion criteria are: (1) daily consumption of tobacco products (including traditional cigarettes, electronic cigarettes, and heated tobacco products) in the past week; (2) age  $\geq 18$  years; (3) owning a mobile smartphone with internet access; (4) staying in Hong Kong during the 1-week EMA study period; and (5) able to read and write Chinese. To confirm the smoking status of the participants, exhaled carbon monoxide will be measured and required to be 4ppm or above, or saliva cotinine to be 30ng/ml or above. Because the proposed study aims to promote smoking cessation in smokers who do not plan to use smoking cessation aids, we will exclude smokers who (1) plan to use smoking cessation services or medication in the coming month or (2) using smoking cessation services, or using nicotine replacement therapy in the past 7 days. Smokers who reported having mental illnesses and female smokers who are pregnant are also excluded as they need more specific smoking cessation intervention.

To date, there have been no randomized controlled trial (RCT) to provide an estimate of effect size for the EMA-based intervention. Our team's previous RCT of testing a personalized smoking cessation intervention showed that the effect size (risk ratio) can be as high as 1.68 (22). Our current outreach health promotion (funded by Health Care Promotion Scheme, project no. 01170418) showed that each month we can recruit 30 to 60 smokers to participate in the smoking cessation RCT. Considering the limited study period covered in this funding application, this proposed study targets to recruit 440 smokers in 11 months.

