## **11. Intervention**

***Smartphone application*** A EMA app will be developed to facilitate documentation of all smoking cues and smoking-related behaviors. After each recruitment, the staff will set up all EMA schedules of the participants in the back-end. Participants can then receive the EMA prompts and complete the EMAs. Participants will use the last 5 digits of their mobile phone numbers as identifier. They will use the app to complete an EoD survey and 4 time-based EMA each day in the 7 consecutive study days.

In each time-based EMA time window, the app will firstly prompt the user to answer questions on the smoking cues, smoking behaviours, and the association between smoking cues and smoking-related behavior, which only takes about 1 minute. If the user does not respond to an EMA prompt, 2 subsequent prompts will be generated. If these additional prompts are not responded to, the EMA will regard nonresponse as missing data. All data will be uploaded to our server immediately after each EMA completion.

The EMA questions on smoking cues cover 3 domains: mood, sleep, environmental triggers. The mood domain includes (1) irritable, depressed, restless, tension, stress, and other emotional cues related to smoking; Sleep domain includes insomnia symptoms for the last night. Environmental triggers include (1) social gathering; (2) family/friends/partner smoking; receive tobacco products/encouragement from others; (3) any other environmental smoking cues. Smoking-related behaviors include (1) nicotine craving (2) whether he/she has bought/consumed tobacco (traditional cigarettes, heated tobacco products and electronic cigarettes) in the past 3 hours (yes/no), (3) whether the tobacco consumption has been due to the exposure to the pro-smoking cues, and (4) other reasons of tobacco consumption (e.g., kill time, habit, leaving a place where smoking is not allowed). EoD survey includes (1) daily tobacco consumption; (2) time to consume the first cigarette after waking; (3) all EMA questions; (4) tobacco control policy questions which include daily exposure to health warnings on their tobacco pack/POS tobacco display/exposure to hotspot.

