#### **14. Statistical analysis**

Intention-to-treat approach will be used to include all consented participants in the analysis and assume non-respondents at the 3-month follow-up as smokers. Chi-squared and t-tests will be used to compare sociodemographic and smoking characteristics of participants to assess the balance between intervention and control group.

The primary comparison is the prevalence of tobacco abstinence and the score of IBC-S between the EMA-based smoking intervention group and the control group. Logistic regression model and linear regression will be used to compare the 7-day PPA and the score of IBC-S between intervention and control group at 3 months, respectively. We will also use multiple logistic regression and multiple linear regression adjusted for imbalance socio-demographic smoking characteristics assessed at baseline to account for imbalances in baseline characteristics.

We will transfer checklist options of smoking cues to binary outcomes. For example, an EMA question asked 'In the past 3 hours, have you been exposed to (check all that apply)' followed by these checklist options: family smoking; friends smoking; partner smoking; receive tobacco products from others; receive encourage of smoking from others). We will recode response into a series of dichotomous variables. Generalized estimating equation analysis will be used to examine the causal relationship between smoking cues and smoking-related behaviors in all participants. A linear mixed model will be used for the association analysis when the outcome is not binary.

Direct operating costs will include app development, salary (of nurses and research assistants), recruitment, telephone follow-up, and publicity items. Costs for study design, analysis, report

writing, and irrelevant administration will be excluded. The cost per successfully recruiting a smoker to participate will be calculated by dividing the total cost by the number of smokers who have joined. Similarly, cost per participant who use smoking cessation aids and per quitter at 3-month follow-up will be calculated.

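### Aim 2 reads policy-cue associations as causal, but a participant's own buying or smoking can produce the recorded exposure to displays, hotspots and pack warnings

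*Protocol*

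**What the plan says.** Protocol section 2 sets Aim 2 as an association between cues and behaviours. On the cue side, "Smoking cues include exposure to POS tobacco displays, health warnings, scenes of others' smoking" and several others are listed. On the outcome side, "Smoking-related behaviors include purchase of tobacco, tobacco consumption, and nicotine craving".

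Section 11 describes the measurement. The 3-hourly prompts cover mood, sleep and environmental triggers, and ask whether tobacco was bought or consumed in the past 3 hours. The policy cues are not named there. They appear in the end-of-day survey, as "daily exposure to health warnings on their tobacco pack/POS tobacco display/exposure to hotspot". The same survey records the day's consumption and repeats the prompt questions.

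Section 14 states the analysis: "Generalized estimating equation analysis will be used to examine the causal relationship between smoking cues and smoking-related behaviors in all participants". It gives no lag for these cues and no way of handling exposure that follows from the behaviour.

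Section 4 wants results of this kind for evaluating tobacco control policy. It also reports a pilot in which POS displays (OR 19.55) and health warnings (OR 14.27) "were significantly associated with subsequent purchase of tobacco, consistent with other EMA observational studies".

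**The concern.** For the three policy cues, the outcome can generate the exposure. A person who buys over a counter stands in front of the display. A person who smokes handles the pack that carries the warning. Section 7 describes a hotspot as an urban place with a butt collector where smokers cluster, so going out to smoke can be the reason for being there. The protocol describes no item that separates this exposure from exposure met independently.

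The analysis could then credit displays with causing purchase, or link warnings to more purchase and smoking, when neither cue changes behaviour. Neither the size nor the sign of such an estimate would answer the policy question. The missing distinction also has to be collected at the time, because no later model can recover it.

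**Working it through.** The protocol gives no planning figure for Aim 2, so there is none to reproduce. The check asks what odds ratio appears for POS display and same-day purchase when the display has no effect. Same-day pairing is assumed, because section 14 states no lag.

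**Inputs (both assumed)**
- q: probability of reporting display exposure on a day without a tobacco purchase.
- r: probability that a purchase itself produces a reported exposure.

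**Formula under no cue effect**
- P(exposed | no purchase) = q
- P(exposed | purchase) = 1 − (1 − q)(1 − r)
- The ratio of the two odds simplifies to OR = 1 + r / [q(1 − r)]

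**Results**

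| q | r | P(exposed given purchase) | OR with no effect |
|---|---|---|---|
| 0.5 | 0.5 | 0.75 | 1 + 0.5/0.25 = 3.0 |
| 0.3 | 0.5 | 0.65 | 1 + 0.5/0.15 = 4.3 |
| 0.3 | 0.8 | 0.86 | 1 + 0.8/0.06 = 14.3 |
| 0.5 | 0.9 | 0.95 | 1 + 0.9/0.05 = 19.0 |
| 0.2 | 0.8 | 0.84 | 1 + 0.8/0.04 = 21.0 |
| 0.2 | 0.9 | 0.92 | 1 + 0.9/0.02 = 46.0 |

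Over q from 0.2 to 0.5 and r from 0.5 to 0.9, the range is 3 to 46.

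**Simulation at the trial's scale.** This used 440 participants (section 7) over 7 days (section 6) and a binomial GEE with independence working correlation and robust standard errors, with 40 replicates per scenario. Further assumptions were 70% end-of-day completion, a 35% daily purchase probability, and a between-person SD in purchase rate of 0 or 1 on the logit scale. The true cue effect was zero throughout.
- Same-day cue, r = 0: mean OR 1.05 (SD 0) and 0.99 (SD 1), with rejection in 15% and 7% of replicates. With 40 replicates these rejection rates are coarse.
- Same-day cue, r = 0.3 and q = 0.3: OR 2.4 to 2.5, with rejection in every replicate. Every scenario with larger r also rejected in 100%.
- Previous-day cue, r of 0.3 or more, SD 0: OR 0.96 to 1.01.
- Previous-day cue, r of 0.3 or more, SD 1: OR 1.18 to 1.58, with rejection in 28% to 100% of replicates.

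A one-day lag therefore removes the artefact only if people do not differ in how often they buy. If they do, frequent buyers have both more exposure and more purchases, and some bias remains. Within-person centring is aimed at that remainder, but the simulation did not test it.

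**The case against.** The strongest case on the other side has five parts.

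- **Item wording is not shown.** Section 11 gives topics for these questions, not their text, so the final items might already make the distinction. This stands as a limit: the point is that the protocol describes no such separation.
- **The overlap is not complete.** A reader might infer that each policy cue contains the outcome event by definition. That nearly holds for warnings on one's own pack. It does not hold for displays and hotspots, which can be met without buying or smoking.
- **The pilot proves nothing here.** A reader might take 14.27 and 19.55 as evidence that the pilot found an artefact, since both fall inside 3 to 46. The protocol does not support that. The pilot used paired assessments and reports purchase after exposure, whereas the model is same-day. With q and r free, a range this wide would cover most large odds ratios. The pilot's display odds ratios for craving (1.57) and consumption (1.47) were modest and not significant. The pilot is compatible with the mechanism and no more.
- **An analysis plan could add lagging and centring.** True, and both would help. Section 4's argument that measurement at different times settles the order of events is weak for a cue reported once for the whole day, and section 4 also prefers separate assessments to the pilot's pairs. Analysis still cannot separate the two kinds of exposure if the app does not collect them.
- **The modelled scope is narrow.** Only displays and purchase are computed. In daily smokers, own-pack exposure and daily consumption are both likely to be near-universal, so a yes/no association between them could hardly be estimated at all. Section 7 lists hotspots as one of several recruitment routes without proportions, so nothing can be built on how many participants come from them.

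**Conclusion.** The point holds for three cues in the non-randomised second aim. As the protocol describes the measurement, a same-day association of POS displays, hotspots or own-pack warnings with purchase or consumption cannot be read as an effect of the cue. For displays and purchase, the odds ratio with no effect is about 3 to 46 under the assumed q and r and same-day pairing. No size has been computed for warnings, hotspots, consumption or craving.

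A reader might infer that the whole of Aim 2 fails. The protocol does not support that. The mechanism has been shown only for the policy cues, and the mood, sleep and social cues are measured differently. The randomised comparison in Aim 1 is not touched.

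**What to change.** In the end-of-day survey, keep the all-exposure items and add two yes/no follow-ups:
- POS display: was any of this when you had not gone in to buy tobacco?
- Hotspot: was any of this when you had not gone there to smoke?

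In section 14, use only these independent exposures as the display and hotspot cues for purchase and consumption in the Aim 2 GEE. Preferably take the cue from the day before the outcome and centre it within person, because the new items alone do not order cue and behaviour within a day.

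Report own-pack warnings, and the all-exposure versions of the other two cues, as descriptive associations, and drop the causal wording for them. The warning item should not be narrowed in the same way: excluding the moment of taking out a cigarette would remove the time when an on-pack warning is normally seen.

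The cost is two short items in an app that section 11 says is still to be developed, and a small edit to section 14. The drawbacks are some recall of intent at the end of the day and wider confidence intervals, because independent exposures are rarer. The widening has not been computed.

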### 3. Estimated duration and commencement data

Proposed starting date: 1 January 2021

Proposed study completion date: 31 December 2022

Expected final report date: 31 December 2022

### 4. Scientific / historical background

***Tobacco control in Hong Kong*** Smoking is the leading cause of morbidity and pre-mature

mortality (1, 2). In Hong Kong, smoking kills 7,000 people each year (3), but there are still more than 620,000 daily smokers (4), half of whom will die prematurely due to smoking (5, 6). With stringent implementation of multi-pronged tobacco control policies in Hong Kong (7), the smoking prevalence has decreased by more than 50% from 23.3% in 1982 to 10.0% in 2017 (4). The government aims to further reduce the prevalence of adult current smoking to 7.8% by 2025 (8). However, the decreasing trend has slowed down since 2000 compared with that in the 1980s-2000 (4), and over half the smokers have no intention to quit (4). Therefore, new and effective strategies are urgently needed to achieve the single-digit target of smoking prevalence.

***Gaps in smoking cessation intervention*** Smoking cessation services and prescription medications are either free or at very low out-of-pocket expense. Further, a telephone quitline is operated by the Department of Health. However, approximately 97% of current smokers have never used effective cessation aids, including counseling services and medication, in their quitting (4), with most quit attempters relying on self-determination (9). According to the Food and Health Bureau, only 25,745 smokers in 2016 availed smoking cessation services under Hospital Authority and services funded by the Department of Health, which is far below the number of quit attempters (113,800 in 2017) estimated by the Thematic Household Survey of Census & Statistics Department (4). Due to nicotine craving and environmental temptations, unaided quitting is very difficult (10). The low usage of current smoking cessation services and the preference of quit attempters suggest that simple interventions that support self-determination may meet the need of those who cannot afford the time for counselling or have low motivation for medications. Unfortunately, clinical trials on unassisted interventions (e.g., policy or low-intensity treatments) are scarce compared with those on assisted cessation intervention (e.g., medication or behavioral intervention) (11). Current smoking cessation services fail to support these smokers to quit and bring them to use effective cessation aids.

***Gaps in tobacco control*** Key tobacco control policies (i.e., tobacco tax, extension of smoke-free areas, ban on tobacco advertising, and the new 85% health warnings on cigarette packs) have been implemented in Hong Kong, but more need to be done. Tobacco tax has not been raised for 5 years since the small increase of 11.7% in 2014, and cigarettes are now much cheaper in Hong Kong than in many developed countries. Seven countries have adopted tobacco plain packaging,

and at least seven (including Macau) countries/regions have banned tobacco displays in retail outlets. Also, widespread use of e-cigarettes and heated tobacco products risks renormalizing tobacco smoking as some users may eventually turn to combustible cigarettes. Unfortunately, the Hong Kong government has not yet passed new tobacco control measures in the above areas. Current cross-sectional studies (i.e., Thematic Household Survey and the Hong Kong Council on Smoking and Health [COSH] opinion survey) are insufficient to show causality between policy implementation and smoking behaviors, and hence new tobacco control measures are always criticized due to lack of local evidence. New research is needed to facilitate valid and accurate observations to inform and evaluate the effectiveness of tobacco control policies.

***Ecological Momentary Assessment (EMA)*** EMA is a self-administered documentation of real-time data describing behavior, cognition, or event in the real world (12). EMA aims to understand “what is going on” close to the moment of assessment or over the very recent past; hence, such measurements have lower recall bias than traditional surveys (13) and are less subject to social desirability bias than reporting pervasive and negative behaviors over a longer period (14). EMA has the advantage of frequently collecting data at multiple time points in the natural environment, which is particularly useful to measure volatile additive behaviors and cognitions like tobacco use (12).

Three types of EMA have been commonly used for tobacco research (12). First, “event-contingent” assessment is used to yield data triggered by an event of interest and can be either initiated by subjects or automatically documented by sensors (e.g., Global Positioning System [GPS]). However, achieving high compliance of subject-initiated EMA is difficult as it relies on participants to actively input data and may pose large burden to the participants. Meanwhile, the accuracy of sensor-based EMA such as wristbands to recognize smoking and GPS is still emerging. The second type of EMA is “signal-contingent/time-based” assessment, which requires subjects to pre-schedule assessments at certain times or at random time in scheduled time blocks. The last type of EMA is to complete one retrospective assessment on previous behaviors and attitude at one particular time of a day (e.g., end-of-day [EoD] survey before night sleep). Time-based EMA and EoD survey will be applied in this proposed research because these assessments minimize subjects’ burden and time, and the cost of instrument development is

lower.

EMA is a valid measurement tool to understand smokers' nicotine craving (15, 16) and environmental cues (17, 18). Measurements at different time points help clarify temporal and causal relationship between event exposures and smoking-related outcomes (12). For instance, EMA studies have revealed how nicotine craving is precipitated by internal stimuli like stress, depressed mood, negative affect, and pain. Another major research direction is to examine the effect of contextual factors on purchase and consumption of tobacco, such as tobacco marketing, health warnings, and alcohol use, using EMA data. Hence, the findings from EMA should have greater impacts on policy implementation than previous retrospective and cross-sectional studies.

***Proposed research*** This research proposal is to make use of EMA for developing personalized smoking cessation interventions and for tobacco policy evaluation. As a policy evaluation tool, EMA allows more accurate data collection of real-world environment, subject to lower recall bias and social desirability bias. Another potential breakthrough is to develop a personalized quit plan and reminders based on EMA of each participant. EMA has been shown as a reliable instrument for documenting real-world smoking and quitting behaviors, which are useful for smoking cessation counselors to design a treatment plan incorporating medication and self-help behavioral interventions. A previous study showed the feasibility of delivering smoking cessation intervention using EMA (19), but no studies have evaluated the effectiveness of EMA-based and personalized interventions. Such EMA-based intervention protocol, if effective, will attract many more smokers to receive a personalized quit plan, without the need to attend multiple smoking cessation counseling sessions, and may motivate them to use effective cessation aids.

Previous EMA-based observational studies usually require participants to complete high-intensity EMA, which included at least 2-week EMA and 4 to 5 times of data collection on each day. These studies provided high amount (around US\$80-230) of financial incentive to sustain an acceptable level of EMA. This EMA design may not be applicable in this proposed research, which aims to motivate smoking cessation but not only for observational study. We require sufficient real-world information about participants' smoking pattern for delivering personalized smoking cessation intervention. Prolonged data collection may reduce participants' motivation to

comply. Further, a high amount of incentive is not preferred as it may reduce the generalizability and induce bias in participation. Hence, we decided to develop a low-intensity EMA in this proposed research.

***Pilot study*** I have conducted a pilot study (first in Asia) to examine the feasibility of using low-intensity EMA for documenting smoking cues and smoking-related behaviors (See additional materials). In total, 302 smokers installed the EMA app (designed by the primary investigator) in their own smartphone for a 2-day data collection and contributed 1,744 EMA (48% of all EMA prompts) and 693 valid EMA pairs for further analysis. The completion rate of 4+ and 6+ EMA pairs in the overall participants was 29.1% and 13.2%, respectively. Findings showed that exposure to tobacco point-of-sale (POS) displays (odds ratio [OR]=19.55,  $p<.01$ ) and health warnings (OR=14.27,  $p<0.02$ ) were significantly associated with subsequent purchase of tobacco, consistent with other EMA observational studies. Exposure to the POS displays apparently led to subsequent craving (OR=1.57) and tobacco consumption (OR=1.47), but the sample size was not sufficient to show statistical significance. Findings were presented in the International Symposium on Digital Health 2019 (20).

During Jan 2020 to Oct 2020, I conducted another pilot study using EMA to investigate exposure to alcohol advertisements and alcohol drinking culture in university students. Participants completed 5 regularly prompted EMA surveys with an EMA app in their smartphone every day for 14 consecutive days. The results showed that the 48 participants responded in 2474 EMA (73.5% of all EMA prompts). The compliance rate of 49+ (70%) and 56+ (80%) EMA was 70.8% and 45.8%, respectively.

These two pilot studies suggests several improvements to increase the EMA compliance: (1) Complicated steps to set up an EMA schedule with the EMA app increase participants' burden in real-world participation. Future app development should reduce these complicated steps and use a more user-friendly interface. A simpler set-up procedure can also save recruitment time for each participant in the outdoor environment, as their available time for recruitment is limited. (2) To sustain a higher EMA compliance for time-based system-triggered EMA, separate assessments (in the alcohol EMA pilot study) is more preferred than pair-based assessments (in the tobacco pilot

EMA). Meanwhile, a cumulative incentive was efficient in improving the compliance rate. (3) Higher but manageable intensity for EMA is needed. Smoking cessation nurses need additional smoking information (e.g., influence from peer or family, stress, depressed mood) to assess nicotine dependency and specific smoking-related cues. Also, more days of EMA may increase the chance of capturing infrequent contextual exposures. Therefore, the days of time-based EMA will be increased from 2 to 7 days. EoD surveys will also be included for assessing daily tobacco consumption throughout a day.

